## Abstract

**Background:**

In palliative care contexts, support programs for families with a severely ill parent and minor children are few, and even fewer have been evaluated scientifically. The aims of this study are to examine feasibility and potential effects of a modified version of the Family Talk Intervention (FTI) in palliative care.

**Methods:**

This ongoing family-centered intervention has a quasi-experimental design comparing one intervention and one comparison group. The intervention includes severely ill parents who have minor children (aged 6–19 yrs) and are receiving advanced homecare in Stockholm, Sweden between March 2017 and March 2018. The main goal of the FTI is to support family communication through psycho-education and narrative theory. The modified FTI consists of six meetings with family members, and is held by two interventionists. Each family sets up needs-based goals for the intervention. For evaluation purposes, data are collected by questionnaire before the intervention, within two months after baseline, and one year after baseline. Interviews will be conducted within two months after FTI is completed. Notes taken by one of the interventionists during the family meetings will also be used. Questionnaire data analysis will focus on patterns over time using descriptive statistics. For interview data and notes, content analysis will be used.

**Discussion:**

This study will add knowledge about palliative care for parents who have minor children. It will contribute by testing use of FTI in palliative care, and point out directions for future evaluations of FTI in palliative care settings.

**Trial registration:**

ClinicalTrials.gov Identifier NCT03119545, retrospectively registered in April 18, 2017.

## Background

There are few evaluated interventions that focus on families where a parent of minor children is being cared for in palliative care [1, 2]. Of these interventions, most are therapeutic with focus on grief [2]. The present study is the first to evaluate a modified version of the Family Talk Intervention (FTI) in specialized palliative homecare in Sweden and directly targeting families where a parent with minor children is severely ill.

FTI initially derives from the psychiatric context and targets families where a parent has an affective disorder. The intervention is family-centered and aims to help the family develop new perspectives on the illness, communicate among themselves, and to support the parent-child relationship [3, 4]. Modified forms of FTI have been evaluated in the context of somatic disease, and shown to alleviate psychiatric symptoms among parents [5]. Parents also described gaining insight into their children’s thoughts and reactions, reduced conflicts and increased family communication [6]. The children described that the intervention helped them feel more secure, increased their knowledge about the illness, and lessened their negative feelings [7].

Guilt and fear of having caused the parent’s illness is common among children and adolescents living with a parent who is severely ill. These feelings may arise because of insufficient or unsuitable information for children. When children do not receive enough information regarding their parent’s illness or death, they often fantasize to fill in the gaps. These fantasies are not always realistic and could exacerbate the child’s fear or worry [7–9].

Children and adolescents with seriously ill and dying parents have an increased risk for mental illness, e.g. long-term depression [10], anxiety [10, 11], sleeping problems, behavioral issues and problems in school [12]. Living with severe illness and also having minor children, naturally affects parenthood. Parents, just like their children, experience guilt, for instance because of lack of energy and time to be with their children. These parents also have a lot of thoughts about how their illness affects their children and wonder about the short- and long-term impact the imminent death might have on them [13, 14].

## Methods/design

### Aims

The aims of this study are to examine the feasibility of using a modified version of the FTI in palliative care (Aim 1) and to explore potential intervention effects on family communication, knowledge about the illness and psychosocial well-being among participating family members (Aim 2).

### Study design

This is a complex intervention study with several interacting components, in a specific setting and tailored to fit these circumstances [15], namely among families where a parent with minor children is severely ill and needs palliative care. The study has a quasi-experimental design, with non-randomized subject allocation. It involves an intervention group that will have the modified FTI and a comparison group that will receive standard care. Mixed-method will be used.

### A modified version of the family talk intervention

FTI is not a psychotherapeutic intervention; rather, the goal is to open up to honest and family-centered communication and is based on psycho-education and narrative theory [3, 4, 16, 17]. The original intervention entails up to 11 meetings [4], but for this study, FTI has been slightly modified, in close cooperation with two interventionists with experience of working with FTI in clinical practice in palliative care. To adjust for circumstances in the palliative context, e.g. shortage of time for the family and a challenging situation for all family members, the intervention is shortened to six meetings (Table 1), and two interventionists work in pairs with the family. The interventionists follow a manual that covers the content of the FTI. In this manual (called the logbook) the interventionists take notes from every meeting. Each meeting lasts 1–2 h and is held once a week at a place chosen by the family. The two interventionists are trained to conduct the FTI, and also have extensive experience of working with FTI in palliative care among families where a parent is severely ill. The modified version of FTI has been found manageable and satisfactory in clinical practice for families and interventionists in this context but it has not previously been evaluated scientifically.

**Table 1 Tab1:** The Family Talk Intervention: the focus at each meeting and the family members involved

Meeting 1–6	Involved family members	Focus at the meeting
Meeting 1	Parents	The ill parent’s history.
		To set up the family’s goals for the intervention.
Meeting 2	Parents	The well parent’s history.
Meeting 3	Each child (preferably without the parents)	The child’s understanding of the illness and the situation, worries and questions
Meeting 4	Parents	Summary about worries and questions from meeting 3.
		Planning the family talk (meeting 5).
Meeting 5	Parents and children	“The family talk”. Preferably led by the parents and consisting of questions from both children and parents.
Meeting 6	Parents and sometimes children	Follow-up with focus on how to communicate within the family in the future to reach the family’s goals.

### Inclusion criteria

For a family to participate in this study, at least one parent needs to be severely ill with palliative care needs, and receiving specialized homecare. The family must also include at least one child aged 6–19 years, but all children in the family are welcome to participate. The family members must speak and understand Swedish. The ill parent defines his/her own family. The family can therefore include partners, grandparents, friends, step-children, ex-partners, or others defined by the ill parent.

### Settings and participants

Recruitment of families is ongoing since March 2017 and will continue until March 2018. Families are recruited through four specialized homecare units in the Stockholm region, all of which have multidisciplinary teams and offer 24-h services. Two units recruit families for the FTI and two units recruit families for the comparison group. All families that meet the inclusion criteria are identified by a social worker at each unit. Families in the intervention group are contacted by phone by the interventionists to set up a meeting where the families are given both oral and written information. Families in the comparison group receive an information letter by post, and one week later they are contacted by phone by one of the researchers.

### Sample size

We expect a sample size of 30 families, based on discussions with the four home care units, about how many patients with minor children that have been enrolled previously at the units. No power is calculated to estimate sample size because it is a small-scaled study and designed as a pilot with no aim to do any hypothesis testing [18, 19].

### Measurements

Feasibility and potential effects are measured by study-specific questionnaires at three time-points. Baseline is placed before intervention start (intervention group) or upon enrollment to advanced homecare (comparison group). The first follow-up is within two months after intervention completion (intervention group) or two months after baseline (comparison group), and the second follow up is one year after baseline. Interviews are held within two months after intervention completion (intervention group). Both the questionnaires and the interviews will focus on the family members’ experiences of participation in the FTI. Collaboration with the contact persons at the units and the interventionists’ experiences of feasibility will be evaluated by observations and interviews.

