Interpreting the outcomes of this study may be hampered by the many confounding factors involved, such as different family constellations, a wide spread of age of children (6–19 years), differences in diagnosis, illness progression and variations in health status and psychosocial well-being of all family members before diagnosis. However, the use of mixed methods could be seen as a strength, as it gives a deeper understanding of the evaluation, the process, outcomes and potential barriers [36, 37]. Quantitative and qualitative data will complement each other and give a greater understanding of the feasibility of the modified version of FTI in palliative care and in studying the potential effects on family communication, knowledge about the illness and the psychosocial well-being among family members.

Children’s voices are often heard only at second hand, through parental proxy reports, even though studies show poor agreement between parents’ and children’s reports [38]. Approaches that include children as subjects, rather than objects, is becoming increasingly common in research involving children [39]. Few studies have been conducted based on children’s own voices during the process of having a parent with severe illness. This study intends to capture the children’s own voices through questionnaires and interviews, as their experiences are an important part of the whole family experience.

This first evaluation of use of the modified version of FTI in families where a severely ill parent with minor children is receiving palliative care, will help to reduce the knowledge gap concerning interventions for these families. The results may also provide important information regarding feasibility and to what degree it is possible to involve all family members at a time in life when most things are put to an end. The proposed study will hopefully point out directions for further evaluations of FTI in palliative care, and for families in these kinds of situations.

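### Baseline is tied to a different event in each arm, so time since homecare enrolment may differ between the FTI and comparison families

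*Protocol article*

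**What the plan says.** The Measurements section of the protocol article gives each arm its own time origin: "Baseline is placed before intervention start (intervention group) or upon enrollment to advanced homecare (comparison group". The later visits depend on it. For follow-up 1 the rule is "The first follow-up is within two months after intervention completion (intervention group) or two months after baseline (comparison group". For both arms, "the second follow up is one year after baseline". Table 2 and the section on psychosocial well-being place the PG-13 grief measure for bereaved family members at that last visit.

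The Inclusion criteria apply to both arms and ask that "at least one parent needs to be severely ill with palliative care needs, and receiving specialized homecare". They set no minimum or maximum time since enrolment.

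Allocation is non-randomized and by unit: "Two units recruit families for the FTI and two units recruit families for the comparison group". The recruitment routes differ as well. In one arm, "Families in the intervention group are contacted by phone by the interventionists to set up a meeting"; in the other, "Families in the comparison group receive an information letter by post, and one week later they are contacted by phone".

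The Data analysis section plans a descriptive comparison within the FTI group and between the groups, separately by age group and family role. The Sample size section expects 30 families and rules out hypothesis testing. The Discussion lists "differences in diagnosis, illness progression and variations in health status" among the confounders, without linking them to how baseline is defined.

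**The concern.** A comparison of change over time needs the same time zero in both arms. Here one clock starts when homecare starts, and the other starts at some point before the first FTI meeting. If the second point tends to come later, FTI families are further along in the illness when first measured. Knowledge about the illness, family communication and anxiety can plausibly shift as illness advances, so part of any difference in level or change could reflect where the clock started.

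The offset is not confined to baseline. Follow-up 2 is counted from it, so the parent's survival to that visit, and the time since death when PG-13 is completed, also depend on the anchor. A later entry point also leaves out families whose parent died before reaching it.

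Allocation by unit gives no protection, because nothing in the design balances time since enrolment. This is a stated rule that differs by arm, not a detail that an article leaves to a fuller document.

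**Working it through.** No figure in the protocol depends on this rule, so there is none to reproduce. The 30 families are an expectation about recruitment, with no alpha, power or effect size. The check is a reading of the text plus two illustrations.

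**1. The anchors side by side**

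| Item | FTI arm | Comparison arm |
|---|---|---|
| Baseline | Before FTI starts | On enrolment to advanced homecare |
| Limit on time since enrolment | None stated | Implied by the anchor |
| Steps before baseline | Identification, phone call, information meeting | Identification, posted letter, phone call one week later |
| Follow-up 1 | Counted from completion of FTI | Counted from baseline |
| Follow-up 2 and PG-13 | One year from baseline | One year from baseline |

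The FTI anchor only says that baseline comes before the first meeting. It does not say how long after enrolment that may be. The comparison anchor is narrower, but a letter and a one-week wait fit poorly with measurement on enrolment.

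**2. How an offset carries to follow-up 2**

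Let a parent die D weeks after enrolment and let baseline fall L weeks after enrolment. Follow-up 2 is then at about L + 52 weeks, and time since bereavement at that visit is L + 52 − D. For the same date of death, a baseline 8 weeks later puts the family 8 weeks further from the death when PG-13 is completed.

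**3. How many families a later baseline could leave out**

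The documents give neither the lag nor survival, so all inputs here are assumed: exponential survival from enrolment, an extra FTI lag (beyond the comparison arm's own) of 1, 2, 4 or 8 weeks, and median survival of 3, 6 or 12 months, with 52.18/12 = 4.35 weeks per month.

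Share of parents dying within the lag = 1 − 0.5^(lag / median).

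For example, an 8-week lag and a 3-month median (13.0 weeks) give 1 − 0.5^(8/13.0) = 0.346.

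| Median survival | 1 week | 2 weeks | 4 weeks | 8 weeks |
|---|---|---|---|---|
| 3 months | 5% | 10% | 19% | 35% |
| 6 months | 3% | 5% | 10% | 19% |
| 12 months | 1% | 3% | 5% | 10% |

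With an assumed 15 families per arm (half of 30), this is 15 × 0.013 = 0.2 to 15 × 0.346 = 5.2 families.

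The table counts only families lost before entry. If all parents shared one constant risk of death, survival counted from baseline would be the same whatever the lag. It changes when prognosis varies between families or over the illness, which the Discussion's own list of confounders makes plausible.

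**4. Follow-up 1**

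For six meetings held exactly weekly, the last falls 5 weeks after the first. Two months is 8.7 weeks. Follow-up 1 in the FTI arm is then between 5 and 5 + 8.7 = 13.7 weeks after meeting 1, against 8.7 weeks after baseline in the comparison arm. A common baseline would not by itself align this visit.

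**The case against.** The best defence is that the wording permits a timing difference but does not establish one. Both arms share the inclusion criteria, and a social worker identifies eligible families in every unit. Placing baseline before FTI starts does not prevent it from falling soon after enrolment. On the stated recruitment steps, the FTI route is not evidently the slower one. All of this stands, and it is why the point is about a risk that the rule creates.

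Three stronger readings are tempting, and the documents do not support them:

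- A reader might infer that the FTI arm holds only families whose parent lived to start FTI. Baseline comes before the start, no rule excludes a family whose parent dies between baseline and meeting 1, and dropouts are among the things to be observed. The condition is survival to baseline.
- A reader might infer that newly enrolled comparison families are set against long-enrolled FTI families. No section says that FTI families are approached weeks or months after enrolment.
- A reader might infer that the comparison arm loses no one before entry. Those families must also pass through a letter, a one-week wait and a call. Selection differs between arms only if the FTI lag is longer.

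It can also be said that this is a descriptive pilot whose Discussion already warns of confounding by illness progression. That lowers the stakes but does not remove the problem. Bias does not depend on a test being run, the between-group description is a planned result, and the warning does not mention the anchor, which is avoidable.

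**Conclusion.** The point holds as a conditional one. The protocol defines baseline by different events in the two arms and sets no limit on time since enrolment in the FTI arm. Time since homecare enrolment may therefore differ by arm, and with it baseline values, change, parental survival and time since bereavement at follow-up 2. If the FTI baseline comes later than the comparison baseline, the FTI arm is also selected for longer parental survival.

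The size cannot be derived from the protocol. The 1% to 35% range rests entirely on the assumed lags, medians and exponential survival, so the selection could be negligible or material. Without the interval from enrolment to baseline, a reader of the results could not tell which. For a non-randomized pilot without hypothesis tests this is worth correcting, but it does not undermine the study: the feasibility aim is largely untouched, and the exposure lies in the between-group description under Aim 2.

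**What to change.** Define baseline by the same event in both arms: for example, the questionnaire completed at consent, within the same window after homecare enrolment in all four units. State how this fits with the letter and one-week wait in the comparison arm. Record the enrolment and baseline dates for every family, and report time from enrolment to baseline by arm next to the between-group description.

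For families already included, report the same interval. Restricting the comparison to overlapping intervals should be no more than an optional sensitivity check, because about 30 families, already split by age group and role, leave little to discard.

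The cost is amended wording and two dates per family while recruitment is still open. The downside is that a common window may exclude a few long-enrolled families.

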#### Primary outcome

Self-reported family communication will be measured using study-specific questionnaires and interviews.

#### Secondary outcomes

Self-reported knowledge about the illness and self-reported psychosocial well-being (psychosocial well-being for children and anxiety for adults) will be measured using study-specific questionnaires and interviews.

#### Questionnaires

To capture each family member’s experiences, we developed five versions of the questionnaires (children 6–7 years old; children 8–12 years; adolescents 13–19 years; well parent/adult; ill parent) (Table 2). The questions involve background characteristics, knowledge and information about the illness, communication within the family, and psychosocial well-being. Participants in FTI answer questions with focus on feasibility. Specific questions were also developed for the bereaved.

**Table 2 Tab2:** The content of the questionnaires and the different time points

	Children, 6–7 years			Children, 8–12 years			Adolescents 13–19 years			Well adult/partner			Ill parent		
	B	F1	F2	B	F1	F2	B	F1	F2	B	F1	F2	B	F1	F2
*Study specific questions:*															
-Background characteristics	X			X			X			X			X		
-Knowledge about the illness	X	X	X	X	X	X	X	X	X	X	X	X	X	X	X
-Communication within the family	X	X	X	X	X	X	X	X	X	X	X	X	X	X	X
*Standardized questionnaires:*															
-Psychosocial well-being (PedsQL)	X	X	X	X	X	X	X	X	X						
-Anxiety (GAD-7)										X	X	X	X	X	X
If intervention:															
*Study-specific questions:*															
-Expectations and goals with participation				X			X			X			X		
-Feasibility					X			X			X			X	
If bereaved:															
*Study-specific questions:*															
-The parent’s/partner’s death		X			X			X			X				
*Standardized questionnaires:*															
-Grief (PG-13)			X			X			X			X			

^B^Baseline. ^F1^Follow-up 1. ^F2^Follow-up 2

##### Questions about family communication and knowledge about the illness

Due to lack of validated instruments in Swedish that measure family communication and knowledge about illness, we constructed study-specific questions according to the method presented by Charlton [20]. We used questions from earlier nationwide surveys about parents or siblings who have lost a child/brother or sister to cancer [21, 22], and teenagers who have lost a parent to cancer [23]. We also used questions from earlier intervention project [24, 25] for our study.

##### Questions about psychosocial well-being

Anxiety in adult participants will be measured at all three time-points using the Generalized Anxiety Disorder (GAD-7) scale [26]. For the children, the Pediatric Quality of Life Inventory version 4.0 (PedsQL) [27, 28] will be used all three times. Grief among bereaved family members (both children and adults) will be measured one year after baseline with the Prolonged Grief Disorder (PG-13) instrument [29].

##### Questions about study participation and feasibility

At baseline, all family members in the intervention group (except the youngest age group) will be asked about their expectations and goals for participating in the FTI. At the first follow up, all family members, except the youngest, will receive questions about the meeting they participated in, how they perceived sharing their thoughts and feelings, if relations within the family changed and if the FTI matched their expectations.

##### Pre-test and pilot of the study-specific questions

The questionnaires were pre-tested and then sent out to families for validation. The questions were validated with eleven children, seven adolescents, and five adults [20]. If the children did not know any person with severe illness they were asked to think about someone they knew, who either was or had been ill. Parents were asked to observe how long it took for the younger children (aged 6–12) to fill in the questionnaires and also report to the research group if any questions had been difficult for the child to understand or answer. Based on the feedback obtained through this validation process, a new questionnaire was developed for children 6–7 years, as some of these children could not differentiate between the response alternatives. We therefore modified them for this age group based on Pediatric Quality of Life Inventory 4.0 [27, 28], using only three response alternatives, represented by happy, neutral and sad smiley faces. Children over the age of seven were able to handle the four response alternatives that we initially used.

